# SYNOPSIS

| Trial Title | The efficacy of rupatadine in treating dengue: a randomised, double blinded, placebo controlled trial | |
| --- | --- | --- |
| Short title | Efficacy of rupatadine in dengue | |
| Clinical Phase | Phase 2 | |
| Trial Design | Randomised, double blinded, placebo controlled | |
| Trial Participants | Patients with dengue infection | |
| Planned Sample Size | 280 with 140 each in each study arm | |
| Treatment duration | 5 days | |
| Follow up duration | 30 days of illness | |
| Planned Trial Period | 1 year | |
|  | Objectives | Outcome Measures |
| Primary | To determine the proportions of dengue patients who develop DHF when treated with and without rupatadine | Therefore, the reduction of the proportion of individuals who develop fluid leakage (DHF) will be assessed.  Evidence of plasma leakage: evidence of plasma leakage considered as detection of free fluid in the abdomen or by the presence of a pleural effusion by USScan and/or by the presence of a rise in haematocrit of >20% of the baseline. |
| Secondary | Investigate whether rupatadine treatment leads to a. reduction in complications such as liver failure.  b. Reduction in development of shock:  c. Need of colloids:  d. Need of blood transfusion/s:  e. Duration of the illness.  f. Sleep disturbance | Liver function tests, blood clotting, colloid infusion volumes, blood transfusion volumes, length of acute illness, sleep scores. |
| Investigational Medicinal Product(s) | Rupatadine 40mg | |
| Formulation, Dose, Route of Administration | Four 10mg tablets of rupatadine to be given orally, and placebo | |

# ABBREVIATIONS

| AE | Adverse event |
| --- | --- |
| AR | Adverse reaction |
| CDR | Centre for Dengue Research |
| CRF | Case Report Form |
| CT | Clinical Trials |
| DF | Dengue Fever |
| DHF | Dengue Haemorrhagic fever |
| DSMB | Data Safety Monitoring Board |
| ERC | Ethic Review Committee |
| GCP | Good Clinical Practice |
| GP | General Practitioner |
| ICF | Informed Consent Form |
| ICH | International Conference on Harmonisation |
| OPD | Out patients department |
| PI | Principal Investigator |
| PIL | Participant/ Patient Information Leaflet |
| SAE | Serious Adverse Event |
| SAR | Serious Adverse Reaction |
| SCOCT | Sub Committee on Clinical Trials |
| SLCTR | Sri Lanka Clinical Trial Registry |
| SMPC | Summary of Medicinal Product Characteristics |
| SUSAR | Suspected Unexpected Serious Adverse Reactions |
| USJ | University of Sri Jayewardenapura |

# BACKGROUND AND RATIONALE

Dengue viral infections represent one of the most rapidly emerging mosquito borne infections in the world, spreading to many geographical regions and causing almost 100 million apparent dengue infections each year (1). From 2005 to 2015, although the mortality rates due to many infectious diseases decreased, the deaths due to dengue increased by 48.7%, resulting in an estimated 18,400 deaths in 2015 (2). Although there is now a dengue vaccine, which is licenced to be used in individuals over 9 years of age in several countries, it is only recommended in countries with high rates of dengue seroprevalence, due to its varied efficacy (3). Intense monitoring with meticulous fluid control is currently the only option in the management of acute dengue infection, as specific treatments for dengue are not yet available.

Severe dengue is characterized by clinically detectable vascular leak, which can lead to haemodynamic instability and shock. Vascular leakage is a hallmark of dengue haemorrhagic fever (DHF) and is thought to occur due to endothelial dysfunction(4) resulting in increased vascular permeability. We recently reported that platelet activating factor (PAF) is elevated during acute dengue infection and is an important mediator of vascular leak (5). Therefore, we used rupatadine in a phase 2 trial to determine its efficacy in treating acute dengue, as it had PAF receptor blocking activities. The clinical trial was a phase II, randomized controlled study, initially consisting of three arms, which were rupatadine 10mg, rupatadine 40mg and placebo. This study was carried out at a dedicated dengue management unit in a tertiary care hospital in Colombo District, Sri Lanka (Infections Diseases Hospital) in 2015/6. Patients who had clinical features suggestive of an acute dengue infection, with a duration of illness ≤ 5 days, and who did not show any evidence of vascular leak and also tested positive for dengue NS1 antigen were recruited. An interim analysis was carried out after recruiting half of the number of patients (n=120). At the interim analysis, it was found that 40mg rupatadine was safe in acute dengue, and that 10mg of rupatadine did not seem to show any benefit when compared to the placebo, and so the rupatadine 10mg arm was discontinued.

The number of adverse events (AE) were similar in those on rupatadine 40mg and on the placebo and all AE completely resolved (Table 1). Two patients (2.98%) in the placebo group developed a SAE, namely acute liver failure. AE such as hepatitis (ALT>250U/L) was more frequent in those on the placebo as 6 (8.9%) patients developed hepatitis when compared to 3 (4.5%) on rupatadine 40mg. Severe thrombocytopenia (<5×10^9^/L) was seen in one patient in the placebo group. However, thromobocyotopenia and hepatitis are known features of dengue and therefore, unlikely to be due to drugs.

|  | Rupatadine 40mg  N=66 | Placebo  N=67 |
| --- | --- | --- |
| Abdominal pain (%) | 17 (25.7) | 21 (31.3) |
| Vomiting (%) | 21 (31.8) | 21 (31.3) |
| Diarrhoea (%) | 27 (40.9) | 24 (35.8) |
| Hepatitis (%) (ALT>250/L) | 3 (4.5) | 6 (8.9) |
| Low platelet counts  <20 ×10^9^/L (%)  20 to 50×10^9^/L (%) | 12 (18.2)  17 (25.7) | 14 (20.9)  21 (31.3) |
| High ALT (>200 U/L) (%) | 9 (13.6) | 12 (17.9) |
| High AST (>200 U/L) (%) | 14 (21.2) | 18 (26.9) |
| Low white cell count  (<1×10^9^/L) (%) | 0 (0) | 0 (0) |

**Table 1: Adverse events experienced by patients on rupatadine 40mg and placebo**

Although, the overall proportion of patients who developed pleural effusion and ascites was similar in both arms, the mean maximum height of the pleural effusion, was lower throughout the illness in those who were on rupatadine when compared to those on the placebo. We did find a >50% reduction in the mean of the maximum height of the pleural effusion, which was seen on day 8 of the illness in the rupatadine arm (1.7, SD±0.4 cm) when compared to the placebo arm (2.9, SD±1.3 cm). The AST on day 7 of illness was significantly less (p<0.05) in those who were on rupaadine compared to placebo; and rupatadine mildly but significantly reduced thrombocytopenia during the study (Fig 1).

[figure not shown]

**Fig 1:** **Changes in clinical and laboratory parameters in patients on 40mg of rupatadine and placebo**. (A) Height of the pleural effusion was measured by daily ultrasound scan and expressed in time (days) since onset of symptoms. Dotted line represents patients receiving rupatadine (40mg daily, n=66), and solid lines represent those receiving placebo (n=67). (B) Haematocrit was measured daily and expressed as percentage change from the baseline value at presentation. Serum aspartate transaminase levels (C), alanine transaminase (D), and blood platelet counts were measured (E). The bars represent mean and SEM. *P<0.05.

6 (8.9%) patients on the placebo developed significant bleeding, which was considered as any bleeding that was not restricted to the skin. Four of these participants reported per vaginal bleeding (in 3 patients lasting for >3 days), one reported melena and one developed epistaxis. In contrast, 2 (3%) of patients in the rupatadine group developed per vaginal bleeding, which did not last for more than one day. There were no differences in other clinical and laboratory parameters, or the duration of illness in those on the placebo and rupatadine. However, there was a trend for an effect of rupatadine on reducing the overall rise in haematocrits and the rise in ALT.

*Early efficacy of rupatadine*

17 (25.7%) who were assigned to the rupatadine arm and 21 (31.3%) assigned to the placebo arm were recruited at ≤3 days of illness. The overall duration of illness was significantly less in the early treatment group (p=0.03). Of those who were on rupatadine and treated, only one patient (5.9%), developed a pleural effusion, when compared to 6 (12.2%) of those who were recruited later than 3 days (12.2%) (Table 2), but this did not reach significance. Although the proportion of patients who developed ascites was similar, the severity was less in the early treated group in which only one patient (5.9%) developed moderate ascites compared to nine (18.4%) of those who were recruited late. Of those who were recruited early only one (5.9%) patient was given colloids (dextran) in anticipation of subsequent deterioration, when compared to 5 (10.2%) of those who were recruited later. Only one patient (5.9%) had a rise in had the haematocrit rise >20% at some time during the when compared to 8 (16.3%) in the late treatment group.

|  | **Placebo**  **Recruited ≤ 3 days**  **N=21** | **Rupatadine**  **Recruited ≤3 days**  **N=17** | **P value** |
| --- | --- | --- | --- |
| Pleural effusion by Ultra Sound Scan | 3 (14.3) | 1 (5.9) | NA |
| Ascites by Ultra sound scan | 9 (42.8) | 4 (23.5) | 0.3 |
| Extent of Ascites as measured by US Scan  Mild  Moderate | 5 (23.8)  4 (19.4) | 3 (17.6)  1 (5.9) | NA |
| Duration of illness  Median (IQR)  Mean (SD±) | 7 (6 to 8.5)  7.1 (1.8) | 7 (5.5 to 7)  6.3 (1.5) | 0.2 |
| Haematocrit >20% rise from baseline | 4 (19.4) | 1 (5.9) | 0.3 |
| Low platelet counts  <20,000  20,00 to 50,000 | 5 (23.8 )  7 (33.3) | 2 (11.7)  7 (41.2) | NA |
| High ALT (>200 U/L) | 2 (9.5) | 1 (5.9) | NA |
| High AST (>200 U/L) | 6 (28.5) | 1 (5.9) | NA |

**Table 2: Clinical and laboratory features of patients who were on rupatadine on the placebo who were recruited on ≤ 3 days**

Those who were in the placebo arm were more likely to have pleural effusions and ascites, more likely to have their haematocrits rise >20%, more likely to have needed dextran and more likely to have AST levels of >200 U/L. When rupatadine was given earlier, one of the primary end points was met, namely a >50% or more reduction in the fluid leakage, as quantity of fluid leakage as assessed by the degree of ascites (mild or moderate). Furthermore, there was a reduction in the proportion of patients who developed pleural effusions (12.2% late vs 5.9% early), moderate ascites (18.4% vs 5.9%) and a >20% rise in the haematocrit (16.3% vs 5.9%). There were no differences in the clinical outcomes and the duration of illness in those who were recruited early (≤ 3 days of illness) when compared to those who were recruited late to the placebo arm of the study. Although those who were recruited early to the placebo arm were less likely to have ALT levels of >200 U/L, the proportion of patients with AST levels >200 U/L were similar in both groups.

**Safety of rupatadine**

In the phase 2 randomized, placebo controlled trial, 40mg of rupatadine was found to be safe and the number of adverse events (AE) were similar in those on rupatadine 40mg and on the placebo and all AE completely resolved. However, the adverse effects on the liver such as development of hepatitis was less in those who were on rupatadine 40mg, when compared to the placebo. In addition, bleeding tendencies were also less. Since both hepatitis and bleeding manifestations are known features of dengue, these clinical features are unlikely to be due to the drugs.

Rupatadine is an orally available second generation antihistamine known to have long acting dual histamine 1 receptor blocking activities and PAF receptor blocking activities for treatment of allergic disease and chronic urticaria (6, 7). Rupatadine has been shown to be well tolerated in many clinical trials in patients who were treated for allergic rhinitis (8, 9), and off-label doses of up to 40mg/day have shown to be well tolerated in chronic urticaria (10). Rupatadine has not shown cardiac adverse effects even at administration of 100mg in healthy individuals (11) (12). It was shown to have less typical side effects of earlier antihistamines such as somnolence, fatigue, headache, impaired memory and learning and sedation (6). A study which determined the effect of rupatadine on those on lorazepam showed that repeated doses of rupatadine had no effect on psychomotor impairment or subjective performance when compared to a placebo (13).

**Justification**

Dengue infections cause significant mortality and morbidity in Sri Lanka and in many tropical and subtropical countries. The estimated annual global cost associated with dengue is $8.9 billion (14). Intense monitoring with meticulous fluid control is currently the only option in the management of acute dengue infection, as specific treatments for dengue are not yet available. There is clearly a major unmet clinical need for a safe effective therapy that can be realistically used in a practical way in resource-poor communities where the bulk of infections occur. In our recently concluded randomised, placebo controlled, phase 2 trial, we found that rupatadine 40mg was safe and well tolerated in patients with acute dengue, and it reduced fluid leakage and other complications associated with dengue, particularly when given early (≤ 3 days from symptom onset) in clinical disease. Therefore, as the first potential active intervention in the treatment of dengue infection, we believe that the efficacy of rupatadine 40mg should be further evaluated by trials conducted in the outpatient setting.

# OBJECTIVES AND OUTCOME MEASURES

**General objective**

To assess the of 40mg of rupatadine on reduction of incidence of DHF and its associated complications in those with dengue viral infections

**Specific objectives**

To assess the effect of 40 mg of rupatadine in reduction of the incidence of DHF

- To determine the effect of 40 mg of rupatadine on reduction of incidence of complications associated with DHF such as acute liver failure, hepatitis, the need for colloids, significant bleeding manifestations
- To determine if rupatadine reduces the duration of post illness fatigue and sleep disturbances

## Primary Study Endpoints

Reduction in proportion of individuals who are treated with rupatadine who develop DHF (fluid leakage). In our earlier phase 2 study, we found that approximately 25% of hospitalized patients with dengue infection develop fluid leakage when assessed by serial US Scanning. Therefore, the reduction of the proportion of individuals who develop fluid leakage (DHF) will be assessed. As this trial is conducted in an OPD setting, those who are not admitted will considered to only have DF as any patient who is suspected to develop DHF (fluid leakage) will be admitted. By the time of discharge from hospital, as the patient would have recovered at this time point, if the patient had not developed fluid leakage, he/she will considered as not had DHF.

Evidence of plasma leakage will be considered as:

- detection of free fluid in the abdomen or by the presence of a pleural effusion by USScan
- Or by the presence of a rise in haematocrit of >20% of the baseline.

The haematocrit of the patients will be monitored at least three times a day. If the haematocrit at any given time point is >20% of the patients baseline the patient will be considered as having fluid leakage according to the Sri Lanka National Dengue Management guidelines (15). The patients will also be monitored by daily serial ultrasound scans done by the same person using a portable USScanner in the ward. The scans will be recorded and reassessed by a consultant radiologist to ensure accuracy. Presence of fluid in the pleural and peritoneal cavities or a rise in haematocrit of >20% will be considered as evidence of plasma leakage.

Ultrasound scanning will be done in the supine position to assess the peritoneal fluid: in the hepatorenal angle, subdiaphragmatic position, in paracolic gutters and in the pelvis, and patient will be kept seated upright on the examination bed for 2 minutes for all the pleural fluid to gravitate in to costodiaphragmatic recesses and scanned from the back of the chest hands raised up and crossed back of the head, mid and posterior axillary lines and in seated up position.

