**Patient follow up**

All patients will be closely monitored during the trial as they will have to visit the study site (OPD) daily for assessment and for blood tests (FBC) as standard management of patients with dengue infection. 4ml of blood will be taken at the OPD for FBCs which are done at the hospital (NIID) as standard management of patients with dengue. All patients will attend daily, and assessed for presence of dengue warning signs and the blood pressure and pulse rate will be recorded. During the visits we will find out the day the patient recovers from illness as defined by the following criteria.

Day of recovery is defined when **all three** criteria below are fulfilled:

-Patient afebrile for 24 hours

-Platelet counts of >50,000 cells/mm^3^ or a rise of 20% from the lowest value

-Return of the haematocrit to the patient’s baselineIf the patient need to attend any OPD visits after the day of recovery, they will be paid Rs. 500 as reimbursement for travel. In each visit the patients will be assessed and monitored in an identical manner.

They will be asked to come 14 days after the onset of illness and the patients general wellbeing will be assessed by patient reported outcome measures including presence of any sleep disturbances (Annexure 3). At the 14 day follow up visit, a blood sample will be taken (4ml) and will be assessed for the presence of dengue IgM and IgG specific antibodies at the Centre for Dengue Research (CDR), University of Sri Jayewardenapura.

The patient will also be contacted 30 days after the onset of illness, by phone to assess the general wellbeing and presence of any sleep disturbances. At the follow up an interviewer administered questionnaire will be used to find out the post viral fatigue and sleep disturbances as previously used in similar studies (17-19). The modified fatigue scale has been previously used to evaluate post viral fatigue following West Nile virus infection (19), which is a viral infection similar to dengue. A fatigue questionnaire has been previously used to evaluate fatigue following dengue infection(18). Before administering these questionnaires to patients in this study (annexure 1), we will validate both questionnaires in this country by translating both to Sinhalese and Tamil.

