## 8.6 Subsequent Visits

Once the patients are recruited they will be asked to visit the OPD daily for assessment as per National Dengue Management guidelines. During these visits, a detailed medical history regaring vomiting, appetite, how they feel (patient based score), presence of abdominal pain will be recorded. A detailed medical examination will be done and the temperature, heart rate, blood pressure, presence of hepatomegaly or pleural effusions or ascites will be recorded. After examination they will have a FBC done at the hospital and they will be sent home once they are assessed along with the report.

Each patient will be asked to come for 5 visits during acute illness and again 14 days after the onset of illness. The patients will be contacted by phone, 30 days after the onset of illness and a questionnaire will be administered (see follow up described above for details).

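### The primary endpoint counts every non-admitted patient as free of DHF without requiring observation to recovery, and this conflicts with its own haematocrit criterion

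*Protocol*

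**What the plan says.** Under Primary Study Endpoints the protocol states that "those who are not admitted will considered to only have DF", and gives as its reason that every suspected leak leads to admission. The same section gives two ways to establish leakage: free fluid on ultrasound, or a haematocrit rise. On the second it says: "If the haematocrit at any given time point is >20% of the patients baseline the patient will be considered as having fluid leakage". The ultrasound is described as "daily serial ultrasound scans done by the same person using a portable USScanner in the ward". No scan is planned for outpatients.

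Outpatients have a full blood count at each daily visit (Trial Design; 8.6 Subsequent Visits). Under Patient follow up, "All patients will attend daily, and assessed for presence of dengue warning signs", and the day of recovery is identified at those visits by three criteria. Section 8.6, by contrast, says "Each patient will be asked to come for 5 visits during acute illness".

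Patients who can no longer swallow the drug (IMP Description) or who no longer wish to take it (9.3 Compliance) are removed from the study. Inclusion in Analysis keeps a lost patient's data up to the point of loss. The missing-data section only describes how much is missing. Neither assigns a primary outcome to a patient who is lost.

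**The concern.** A binary endpoint needs a rule for saying that the event did not happen. Here the rule is the absence of an admission, not the observation of a course without leakage. Three consequences follow.

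- A patient who is never admitted and whose follow-up stops early is a non-event if the rule is taken literally.
- An outpatient whose blood count shows a rise above 20%, but who is not admitted, is DHF under one sentence and DF under another.
- Ultrasound evidence exists only for admitted patients, and admission is itself something the drug is expected to change. Trial Design lists the proportion admitted among the secondary endpoints, and Expenses and Benefits says that treatment could reduce the need for admission. A difference between arms in admission or in loss can therefore appear as a difference in DHF.

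**Working it through.** **The two rules side by side.** Take an outpatient with a rise above 20% who is not admitted.

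| Rule in Primary Study Endpoints | Result |
|---|---|
| Haematocrit criterion, any time point | DHF |
| Not admitted | DF |

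Nothing says which prevails. For a never-admitted patient who stops attending, the admission rule gives DF, while Inclusion in Analysis and the missing-data section give no outcome.

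**What ward-only ultrasound can leave unseen.** In Table 2 (earlier trial, placebo, recruited at 3 days or less), 9 of 21 had ascites and 4 of 21 had a haematocrit rise above 20%. So at least 9 − 4 = 5 of the 9 with ascites did not meet the haematocrit criterion. These figures come from a hospital trial and only illustrate the point.

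**Inputs for the size.** Rates of 42.8% and 23.5% and 10% dropout (The Number of Participants); 140 per arm (Synopsis); alpha 0.05, taken as two-sided. I take 42.8% as the placebo rate, as in Table 2. A 25% control rate is a second assumption, prompted by the roughly 25% quoted under Primary Study Endpoints, with the same risk ratio: 0.235/0.428 = 0.549, so 13.7% on rupatadine.

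**Reproducing the plan.** The text gives no figure for power. At an assumed 90%, two-sided, without continuity correction, n = 123 per arm. Then 123/0.9 = 137, close to the stated 140.

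**Power formula.** Power = Φ[(|p1 − p2| − 1.96·SE0)/SE1], with SE0 = √(2p̄(1 − p̄)/n) and SE1 = √((p1(1 − p1) + p2(1 − p2))/n).

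**Equal 10% loss.** The fair comparator is 140 × 0.9 = 126 observed per arm. Coding the lost as DF instead keeps n = 140 but multiplies both risks by 0.9.

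| Control rate | 126 observed per arm | Lost coded DF, n = 140 |
|---|---|---|
| 42.8% | (0.193 − 1.96 × 0.0593)/0.0580 → 90.7% | 38.5% v 21.2%: (0.1737 − 1.96 × 0.0547)/0.0537 → 89.2% |
| 25% (assumed) | 62.1% | 22.5% v 12.4% → 61.0% |

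The coding rule costs about 1.5 and 1.1 points. The risk difference shrinks by a tenth (19.3 to 17.4 points in the first row) and the risk ratio is unchanged.

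**Unequal loss, no true effect.** With true risk p in both arms and losses d coded as DF, the observed risks are p(1 − d), so the false difference is p × (difference in d). The loss rates are assumptions, with the higher loss placed on rupatadine; n = 140 per arm.

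| Loss, placebo v rupatadine | True risk | Observed risks | False difference | Two-sided rejection |
|---|---|---|---|---|
| 8% v 12% | 25% | 23.0% v 22.0% | 1.0 point | 5.5% |
| 8% v 12% | 42.8% | 39.4% v 37.7% | 1.7 points | 6.0% |
| 5% v 15% | 25% | 23.8% v 21.3% | 2.5 points | 7.9% |
| 5% v 15% | 42.8% | 40.7% v 36.4% | 4.3 points | 11.4% |

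**The case against.** The strongest reply is that the section gives a reason for its rule: every patient suspected of leakage is admitted. On that pathway a clinic rise above 20% raises suspicion, the patient is admitted, and the outcome is recorded as DHF. The clinic examination also looks for effusions and ascites, so outpatients are not unobserved. And "The haematocrit of the patients will be monitored at least three times a day" fits a ward better than a daily clinic visit, which suggests that the haematocrit paragraph had admitted patients in mind. A reader might infer that the admission rule overrides whatever the clinic blood count shows. The documents do not support that. The two sentences collide only when the pathway fails, for example if a patient declines admission. That conflict stands, because the pathway is an expectation and the protocol does not say which sentence then governs.

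Three other strong readings also fail.

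- The protocol does not say that lost patients are coded as DF. That is the literal effect of the admission rule, and the sections on missing data and inclusion leave it unclear.
- A patient admitted to another hospital is not plainly a patient who was not admitted.
- The earlier trial's finding on effusion height, "which was seen on day 8 of the illness in the rupatadine arm", concerns the size of effusions. It does not show that leakage begins after the planned visits end.

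It is also fair to say that the rule is the same in both arms, that the trial is double-blind with a matching placebo, and that only an overall 10% dropout is given. Equal loss dilutes the difference but does not favour either arm. This reply does not cover admission, which the protocol itself expects to differ by arm.

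**Conclusion.** The rule is wrong as written. It turns the absence of an admission into the absence of DHF, requires no observation to recovery, has no exception for loss or withdrawal, and contradicts the haematocrit criterion beside it. Because it sits in the definition of the primary endpoint, this is not a detail that can be left to an analysis plan.

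The size is modest unless the arms differ. Equal 10% loss costs 1 to 1.5 points of power. Comparing 89.2% with the 93.3% that 140 fully observed patients per arm would give suggests a larger cost, but most of that gap is ordinary dropout. The false differences of 1.0 to 4.3 points and rejection rates of 5.5 to 11.4% rest on assumed unequal losses. Nothing in the protocol predicts such losses, and they should be read as a range. The effect of differing admission cannot be put in numbers from the document.

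**What to change.** In Primary Study Endpoints:

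1. Apply the haematocrit criterion to every recorded blood count, clinic or ward.
2. Code DF only when the patient has been followed to the recovery criteria under Patient follow up without evidence of leakage.
3. Otherwise treat the outcome as missing, not as no DHF, and commit to a best-case and worst-case sensitivity analysis. The detailed method can sit in the analysis plan.
4. Add a question on any hospital admission to the day-14 visit and day-30 call, which are already planned.

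Patient follow up and section 8.6 must also be reconciled, so that the observation period for the endpoint is clear. Which schedule applies is for the investigators to decide.

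The cost is some rewording, one added question and one sensitivity analysis. The real downside is that some outcomes will be classed as missing, and the number will depend on how the visit schedule is settled.
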